#### Secondary Endpoint

1.7.2

Topographic maps will be generated for each QEEG feature (e.g., absolute power, relative power, power ratio, peak frequency, amplitude asymmetry, coherence, and phase lag) for both responder and non‐responder groups using Neuro Guide software, then calculate the average QEEG features for each group using Neuro Guide. Subsequently, the statistical significance of the dissimilarity between the two groups' EEG topographic maps will be determined using independent *t*‐tests or the Mann–Whitney *U* test, depending on the normality of the variables. ROC analysis estimating Area Under the Curve (AUC), sensitivity (SN), specificity (SP), positive predictive value (PPV), negative predictive value (NPV), A positive likelihood ratio (LR+), and the negative likelihood ratio (LR‐) for optimal cut‐points, as well as comparing AUC across biomarkers, will be performed using Stata 18 software. These diagnostic accuracy measures specifically assess the predictive ability of QEEG biomarkers in distinguishing responder from non‐responder status.

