**Design:**

This multi‐center, assessor‐blinded clinical trial will examine QEEG biomarkers as predictors of rTMS treatment responsiveness in 25 patients with mild cognitive impairment (MCI). Adults aged 60 years or older will undergo cognitive assessments using the Montreal Cognitive Assessment (MoCA) or mini‐mental state examination (MMSE) and have an electroencephalography (EEG) recording. Participants will complete 10 rTMS sessions targeting the left DLPFC over 2 weeks, with 2000 pulses per session at 20 Hz. Cognitive tests will be repeated post‐treatment, and participants will be classified as responders or non‐responders based on cognitive changes, then baseline QEEG parameters will be compared between the two groups. The primary endpoint is the proportion of responders at ten sessions after rTMS (score post‐intervention > score pre‐intervention = responder, according to the minimal clinically important difference (MCID) threshold (i.e., an increase of at least 3 points or 10% on the MMSE, or an increase of at least 1 point on the MoCA); score post‐intervention ≤ score pre‐intervention = non‐responder). The secondary endpoints are the differences in baseline QEEG features between responders and non‐responders.

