Transcranial magnetic stimulation (TMS) is a non‐invasive brain stimulation technique, a safe method with high tolerability and no major adverse effects such as diabetes, tardive dyskinesia, weight gain, etc. (Lefaucheur et al. 2017; Lefaucheur et al. 2020; Su et al. 2023). Furthermore, cortical excitability, neuroplasticity, and functional connectivity between different brain regions are also altered by repetitive TMS (rTMS) (Wassermann and Zimmermann 2012; Salomons et al. 2014). In TMS, action potentials in neurons can be physically induced by an electromagnetic field or a “pulse” produced by running an electric current through a coil (Barker et al. 1987; Barker et al. 1985). While rTMS has shown promise in improving cognitive function in some individuals with MCI, its efficacy is variable (Yan et al. 2023). Identifying reliable predictors of treatment response would be crucial to optimize treatment selection and improve patient outcomes (Lithgow et al. 2022).

In line with this goal, a 2024 comprehensive meta‐analysis of major depressive disorder research identified frontal theta activity in EEG as the most promising candidate for predicting treatment outcomes (Jin et al. 2024). Building on this finding, ongoing research continues to explore the potential of predictive biomarkers.

Proposed indices of usefulness of magnetic stimulation in major depressive disorder include large spectral power values within the low‐frequency θ2 (6–8 Hz) and α1 (8–9 Hz) sub‐bands in the posterior (parietal‐occipital‐posterior) EEG leads (Iznak et al. 2020), as well as the utilization of artificial neural networks with a sensitivity of 93.33% (Erguzel et al. 2015). Furthermore, it is well‐established that in Alzheimer's disease, the primary component of EEG abnormalities involves alterations in alpha and theta bands (Güntekin et al. 2020). The findings of the 2022 investigation are consistent with this observation, demonstrating that EEG event‐related theta responses may be susceptible to neuromodulation therapies (Kayasandik et al. 2022).

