#### EEG Recording

1.2.2

QEEG is software that quantitatively extracts EEG data for numerical analysis. QEEG parameters: The scalp records the electrical potentials associated with the brain, known as EEG. The four rhythms of delta, theta, alpha, and beta are considered the main frequency bands of brain waves. Delta rhythm covers the frequency range from 1 to 4.0 Hz, theta (4–8 Hz), alpha (8–12 Hz), broad beta (12–25 Hz), and hi‐beta (25–30 Hz). All frequency rhythms take into account the following parameters: absolute power, relative power, power ratio, peak frequency, amplitude asymmetry, coherence, and phase lag.
✓Absolute power: The amount of wave energy in a specific frequency spectrum in the frequency domain.✓Relative power: Divide the absolute power of a specific frequency band by the total absolute power of all frequency bands.✓Power ratio: Divide the power of one frequency band by the power of another frequency band.✓Peak frequency: The peak detection method for computerized EEG analysis involves measuring the amplitude and time interval between successive maxima (peaks) and minima (crossings) in a signal.✓Amplitude asymmetry: There are neuroanatomical differences between the left and right sides of the brain, as well as lateral functional differences, also known as lateralization of brain function. Asymmetry is usually calculated by subtracting the natural logarithm of the left hemisphere‐specific frequency power from the right hemisphere‐specific frequency power natural logarithm while using link ears as the reference electrode.

There are neuroanatomical differences between the left and right sides of the brain, as well as lateral functional differences, also known as lateralization of brain function. Asymmetry is usually calculated by subtracting the natural logarithm of the left hemisphere‐specific frequency power from the right hemisphere‐specific frequency power natural logarithm while using linked ears as the reference electrode.

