We will record the participants' EEG data using a 19‐channel EEG system with passive electrodes (Science Beam; Parto Danesh Co., Iran). It has 19 scalp channels, a sampling rate of 500 Hz per channel, an ADC resolution of 24 bits, and a CMRR of 75 dB at 500 Hz. The electrode placement will follow the 10–20 international norm and referential montage linked ears. Every subject had a 5‐minute resting‐state EEG recording with their eyes open, followed by a 5‐min recording with their eyes closed, all while maintaining an impedance of less than 10 kΩ and applying a 0.5 low‐cut and a 500‐Hz high‐cut filter.

Finally, after the automated algorithm, manual checking by an expert neuroscientist for the artifact rejection process. Topographic maps will be generated for each QEEG feature in the frequency domain (e.g., absolute power, relative power, power ratio, peak frequency, amplitude asymmetry, coherence, and phase lag) for both responder and non‐responder groups using Neuro Guide software version 3.2.1.1 (Loo et al. 2016; Coburn et al. 2006).

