#### Primary Endpoint

1.7.1

All assessors will be blinded to group allocation and receive data labeled as “group A” and “group B.” Statistical analyses will be conducted using StataNow18.5 (Stata Corp, College Station, TX, USA), adhering to CONSORT guidelines. Normality of continuous variables will be checked using skewness and kurtosis, with variables considered non‐normal if absolute skewness > 2 or kurtosis > 3. Baseline characteristics, including (sex, hyper‐lipidemia, hypothyroid, hyper‐tension, diabetes, smoking, ischemic heart disease, education, and age) will be compared between groups using Fisher's exact test for categorical variables and the Mann–Whitney *U* test for non‐normal continuous variables. For normally distributed continuous variables, between‐group comparisons will be performed using the independent samples t‐test.

Initially, paired *t*‐tests (a suitable transformation or non‐parametric test) or equivalents for non‐normal data will be used to evaluate overall pre‐ to post‐rTMS changes within all 25 participants, assessing global treatment efficacy and identifying cognitive subdomains demonstrating the greatest response. Subsequently, participants will be categorized into responders and non‐responders based on MCID criteria. Between‐group comparisons of cognitive scores and subdomains will then be performed using ANOVA for baseline and ANCOVA for post‐intervention outcomes, adjusting for baseline scores and potential confounders. Pre‐intervention values refer specifically to baseline cognitive test scores, totally and in each cognitive sub‐domain, and related continuous variables measured before rTMS, which serve as covariates in the analyses. The QEEG features are analyzed separately as part of the secondary endpoint assessment. For non‐normal variables, suitable transformation will be applied, and median differences with percentage changes reported. Marginal plots from ANCOVA will visualize adjusted group differences post‐intervention. This two‐stage analytical approach allows comprehensive evaluation of rTMS effects both globally and within clinically meaningful responder groups across cognitive domains.

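### Section 1.7.2 tests an open-ended set of QEEG features in 25 patients with no primary feature and no stated error control, so chance biomarkers are likely

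*Protocol article*

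**What the plan says.** The trial is to examine QEEG "predictors of rTMS treatment responsiveness in 25 patients with mild cognitive impairment (MCI" (Abstract, Design). Section 1.6.2 defines the secondary endpoint only as baseline QEEG differences between responders and non-responders. Section 1.2.2 sets out the raw material:

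- **Feature types:** "All frequency rhythms take into account the following parameters: absolute power, relative power, power ratio, peak frequency, amplitude asymmetry, coherence, and phase lag".
- **Bands:** "Delta rhythm covers the frequency range from 1 to 4.0 Hz, theta (4–8 Hz), alpha (8–12 Hz), broad beta (12–25 Hz), and hi‐beta (25–30 Hz". The same section also speaks of four main rhythms.
- **Recording:** "It has 19 scalp channels, a sampling rate of 500 Hz per channel", with five minutes eyes open and five minutes eyes closed.

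Section 1.7.2 then states "Topographic maps will be generated for each QEEG feature (e.g., absolute power, relative power, power ratio, peak frequency, amplitude asymmetry, coherence, and phase lag". The two groups' maps are compared by independent t-test or Mann–Whitney test. An ROC analysis follows, with AUC, optimal cut-points, sensitivity, specificity, predictive values and likelihood ratios, and AUCs are compared across biomarkers.

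No feature, band, site or eye state is singled out. The article gives no alpha, no number of tests and no approach to multiplicity. The list of features opens as a set of examples, so it is not closed.

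**The concern.** With many features, few patients and no ordering among the features, some differences will reach nominal significance even if baseline QEEG has nothing to do with response. The plan does not say which result would count as the answer, so the features that happen to separate the groups would be the ones reported.

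The ROC step adds to this. AUC is the Mann–Whitney statistic divided by the product of the group sizes, so picking the feature with the highest AUC amounts to picking the most extreme test. The cut-point is then tuned and assessed in the same patients.

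Two stated purposes are at stake. The Aims and section 3 set out to identify a biomarker that predicts response. The introduction and section 4 want effect sizes to plan later trials, and an effect size selected as the largest of many is biased upwards.

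**Working it through.** The article states no test count, alpha or expected error rate, so there is no figure to reproduce. The counts below rest on stated inputs plus labelled assumptions.

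**Inputs from section 1.2.2**
- 19 channels, which give 19×18/2 = 171 electrode pairs if every pair is used (assumption; the pair set is not given).
- 5 bands, which give 5×4/2 = 10 possible band ratios. With 4 bands there are 6.
- 7 feature types and 2 eye states.
- Asymmetry is described as "subtracting the natural logarithm of the left hemisphere‐specific frequency power from the right hemisphere‐specific frequency power natural logarithm". Read literally this gives 8 left–right pairs; 171 pairs is the widest reading.

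**Assumptions:** two-sided alpha of 0.05 and no true association for any feature.

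**Formula:** expected false positives = M × 0.05, where M is the number of tests. This mean does not depend on correlation between features.

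**Single-site features, five bands:** absolute 19×5 = 95, relative 95, ratios 19×10 = 190, peak frequency 95; total 475.

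| Reading, per eye state | M | Expected false positives |
|---|---|---|
| One test per map: 6 types × 5 bands + 10 ratios | 40 | 2 |
| Homologous pairs for all paired measures: 475 + 3×8×5 | 595 | 30 |
| Four bands, 8-pair asymmetry, all pairs for coherence and phase lag: 228 + 114 + 32 + 1,368 | 1,742 | 87 |
| Five bands, 8-pair asymmetry, all pairs for coherence and phase lag: 475 + 40 + 1,710 | 2,225 | 111 |
| Five bands, all pairs for all three: 475 + 2,565 | 3,040 | 152 |

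With 40 independent tests, the chance of at least one false positive is 1 − 0.95^40 = 0.87. Both eye states double each expected count, for example 4,450 to 6,080 tests and 223 to 304 expected for the last two rows.

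**Sensitivity**
- At alpha 0.01 the last two rows give 22 and 30.
- The Mann–Whitney test has a size of about 0.04 at a 5/20 split, so 2,225 tests would give about 89.
- One test per feature type (7 tests) would still leave 1 − 0.95^7 = 0.30. Section 1.2.2 takes each type per rhythm, and no such omnibus test is described.
- Correlation widens the spread. In a simple model of 2,225 features in 25 blocks, with correlation 0.6 within blocks, 95% of counts lie between about 40 and 217 around a mean of 111. Without correlation the range is 92 to 132.

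**Best AUC by chance.** Simulated null features, 25 patients, splits from 5/20 to 20/5: the median best AUC is about 0.80 to 0.88 among 100 independent features and 0.89 to 0.97 among 2,225. Correlated features would behave like a smaller number of independent ones.

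**The case against.** **The study is declared exploratory.** The introduction calls it an exploratory pilot seeking preliminary biomarkers. Section 4 asks for caution and rules out definitive hypothesis testing, and QEEG is a secondary endpoint. This lowers the weight of the point. It does not remove it, because the section 4 caveat concerns sample size, group imbalance and power, and never mentions the number of tests. The Discussion still says the findings will help rTMS to be prescribed correctly in MCI.

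**Alpha and multiplicity may be in an unseen analysis plan.** That stands: the article does not say that tests are unadjusted, and a reader should not infer that it does. However, which variable is the endpoint belongs in the protocol, and an adjustment elsewhere would not supply a main predictor. Section 1.7 is detailed enough to give normality cut-offs and likelihood ratios.

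**The testing unit is unclear.** Section 1.7.2 speaks of comparing maps, which could mean far fewer tests than one per site or pair. This is why the result has to be a range.

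**Frontal theta.** A reader might infer that the protocol has one supported hypothesis, since a cited meta-analysis "identified frontal theta activity in EEG as the most promising candidate for predicting treatment outcomes". That work is in major depression. The introduction also cites posterior theta and alpha sub-bands, and the Discussion cites parietal alpha (reduced consciousness) and theta (severe dementia), noting that those last two studies differ from this one in disorder and stimulation. There are several candidates, none of them from MCI.

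**The normality rule.** A reader might also infer that treating variables as non-normal "if absolute skewness > 2 or kurtosis > 3" makes the false-positive problem worse. The document does not say whether kurtosis is raw or excess. Simulated on normal data at n = 25, the rule flags about 29% of variables on the raw scale and about 0.4% on the excess scale. Even on the raw scale it only switches between two valid tests, and the simulated size stays at 0.048 to 0.054. The only question worth asking is which scale is meant.

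**Conclusion.** The point holds as a gap in how the QEEG endpoint is fixed. An open-ended family of features goes to significance tests, and to cut-point and AUC selection in the same 25 patients, with no main predictor and no stated error control. Under two-sided 5% testing and no true association, about 2 to 152 false positives are expected per eye state, depending on the testing unit, bands and electrode pairs. Even one test per map makes at least one likely (87% if independent).

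A reader might go further and conclude that over 100 false biomarkers are certain. The documents do not support that. The count and the 5% level are assumptions, the upper figures need a separate test for every site and all 171 pairs for connectivity, and correlation makes the actual number vary widely. Nor does it follow that the pilot is without use: feasibility and descriptive signal patterns are unaffected. What suffers is any claim to have found a predictor, and the size of the effects carried into later trials.

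**What to change.** In section 1.7.2, before responder status is linked to the EEG data:

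1. Name one QEEG feature, region and eye state as the main predictor and test it at 5%. The choice is the investigators', among candidates that the article cites, such as frontal theta or parietal alpha.
2. List the remaining features, electrode pairs and eye states. Analyse them together with a max-statistic permutation test (permuting responder status over patients) or Benjamini–Hochberg FDR. Report them as exploratory, with effect sizes and intervals.
3. Label AUCs, cut-points and accuracy measures as apparent, or correct them for optimism with feature selection included in the correction.
4. Optionally, state whether the kurtosis cut-off in section 1.7.1 is raw or excess.

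This needs a paragraph of text and a short permutation program, and no new patients or data. The cost is that fewer features will be called significant. Naming one feature keeps usable power: with a 12/13 split and a standardised difference of 1.2, power is 82% at 5%. Bonferroni over 2,225 features (0.05/2,225 = 2.2×10⁻⁵) would leave about 4%, so a blanket Bonferroni correction is not proposed.

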## Discussion

2

In this study, QEEG baseline in MCI patients will be used for the first time to discriminate responders that obtained cognitive improvements after rTMS from non‐responders.

The global prevalence of dementia is predicted to triple in the next three decades (Prince et al. 2016), and currently there appears to be no disease‐modifying therapy or cure for dementia on the immediate horizon (Middleton et al. 2018).

Several studies suggest that rTMS can improve general cognitive function (Kayasandik et al. 2022; Šimko et al. 2022; Koch et al. 2022). However, it is important to note that TMS is a time‐consuming and expensive procedure that requires patients to make daily visits over an extended period of 4 to 6 weeks (Goodman et al. 2024). These factors represent a significant challenge for patients requiring this treatment. Use of the device is ineffective in some individuals, resulting in wasted time for effective treatment of individuals who do not respond. Identifying a QEEG biomarker that can predict recovery prior to intervention would be highly valuable. As the number of FDA approvals for this device increases and interest grows, the importance of predictive biomarkers will also rise. Investigating changes in QEEG parameters related to dementia presents a fascinating area of research within neuroscience.

Research has indicated that in cases of mild dementia, there is an increase in the theta brainwave band coupled with a decrease in the beta brainwave band. As dementia progresses, this pattern is further characterized by an increase in the delta brainwave band and a decrease in the alpha brainwave band (Gandelman‐Marton et al. 2017). The increase in the delta brainwave band corresponds to the white matter shrinking in the frontal region of patients with MCI and Alzheimer's disease (Babiloni et al. 2006). Additionally, the reduction of the alpha brainwave band occurs in the parietal, occipital, and temporal regions, in line with hippocampal shrinkage in MCI and Alzheimer's patients (Babiloni et al. 2009). Furthermore, the use of acetylcholinesterase inhibitors in dementia and Alzheimer's treatment leads to a reduction in the delta and theta brainwave bands (Jelic et al. 1998). Progression of disease and the failure of pharmacological treatments are associated with an increase in the delta and theta brainwave bands and a decrease in the alpha and beta brainwave bands (Jelic et al. 1998). Patients with Alzheimer's disease also show an increase in low‐frequency brainwave band power and a decrease in high‐frequency brainwave band power (Baggio et al. 1991). Additionally, there is a significant decrease in coherence in the theta, alpha, and beta brainwave bands in the frontal regions, which is consistent with the loss of neurons and disconnection of neocortical neurons (Besthorn et al. 1994).

Previous research with similar objectives has shown that patients with reduced levels of consciousness exhibit a higher absolute power of alpha waves in both the left and right parietal regions, which is associated with a greater likelihood of responding to rTMS (He et al. 2020). Additionally, in patients with severe dementia, the difference in the theta band has been observed as a predictor for respondents (Kayasandik et al. 2022). However, these studies differ from ours in terms of the stimulation parameters, including the stimulation site and disorder. Our findings will contribute to the development of correct prescription of rTMS therapy for MCI patients.

Besides, there are some limitations to this protocol study. As an open‐label trial, it is subject to significant confounds, including treatment expectations on the part of participants, but this is a methodological limitation intrinsic to an open‐label trial (Thase 2001). For the future direction, more analysis with a larger dataset will be recommended, and randomized, sham‐controlled study can affect the generalizability and reliability of the outcomes. Additional predictive biomarkers such as genetic factors, neuroimaging, or biochemical biomarkers can be noticed in future study.

## Conclusion

3

This study aims to identify a QEEG biomarker that can serve as a predictor of recovery in patients with MCI before the commencement of the rTMS intervention. The rising concerns regarding the prevalence of significant cognitive disorders, coupled with the deficiency of effective treatment options, have intensified the focus on innovative technologies such as rTMS. However, its time‐intensive and expensive nature often hinders the application of TMS. Consequently, the development of predictive biomarkers that can anticipate therapeutic responses before the intervention is of considerable importance. Our research investigates cognitive improvement following rTMS and examines whether specific QEEG features differ between participants who improved (responders) and those who did not (non‐responders).

